## Abstract

**Background:**

Loss of hand function is one of the most devastating consequences of spinal cord injury. Intensive hand training provided on an instrumented exercise workstation in conjunction with functional electrical stimulation may enhance neural recovery and hand function. The aim of this trial is to compare usual care with an 8-week program of intensive hand training and functional electrical stimulation.

**Methods/design:**

A multicentre randomised controlled trial will be undertaken. Seventy-eight participants with recent tetraplegia (C2 to T1 motor complete or incomplete) undergoing inpatient rehabilitation will be recruited from seven spinal cord injury units in Australia and New Zealand and will be randomised to a control or experimental group. Control participants will receive usual care. Experimental participants will receive usual care and an 8-week program of intensive unilateral hand training using an instrumented exercise workstation and functional electrical stimulation. Participants will drive the functional electrical stimulation of their target hands via a behind-the-ear bluetooth device, which is sensitive to tooth clicks. The bluetooth device will enable the use of various manipulanda to practice functional activities embedded within computer-based games and activities. Training will be provided for one hour, 5 days per week, during the 8-week intervention period. The primary outcome is the Action Research Arm Test. Secondary outcomes include measurements of strength, sensation, function, quality of life and cost effectiveness. All outcomes will be taken at baseline, 8 weeks, 6 months and 12 months by assessors blinded to group allocation. Recruitment commenced in December 2009.

**Discussion:**

The results of this trial will determine the effectiveness of an 8-week program of intensive hand training with functional electrical stimulation.

**Trial registration:**

NCT01086930 (12^th ^March 2010)

ACTRN12609000695202 (12^th ^August 2009)

## Background

The incidence of spinal cord injury (SCI) varies between countries but is estimated at 10 to 83 per million, per year with most injured under the age of 25 years [1]. More than one third of these individuals sustain an injury that causes damage to the spinal cord in the cervical region and results in tetraplegia [1]. Most people with tetraplegia remain wheelchair-dependent and reliant on others for physical care. Importantly, however, limited hand and upper limb function is often more disabling and of greater importance to them than their inability to walk [2,3]. Even modest improvements in hand function can have life-changing implications. For example, a small amount of finger movement enables a person with tetraplegia to use a keyboard, press a switch, scratch the face and turn the page of a book. The ability to do these simple tasks reduces dependency on others, improves potential for employment and enhances quality of life.

There is evidence to suggest that intensive task-specific training can enhance hand function in people with tetraplegia [4,5]. Intensive training with superimposed functional electrical stimulation (FES) may be particularly therapeutic especially in individuals with poor grasp [6-8]. It is believed that this combination of therapies provides the damaged spinal cord with excitation from the sensorimotor cortex along with intensive sensory input from the periphery. Neural bombardment of this kind on the damaged spinal cord may promote neural plasticity and, in particular, may provide the critical stimulus required to elicit neurophysiologic and structural re-organisation of the relevant pathways [9].

Recent advances in computer-game technology provide innovative ways of encouraging patients to engage in intensive task-specific training [10]. Here we describe the protocol for a randomised controlled trial using FES and an exercise workstation (ReJoyce, Rehabtronics Inc. Edmonton, Canada). Patients wear a behind-the-ear blue tooth sensor that is triggered by tooth clicks and sends radio signals to a customised muscle-stimulator garment worn on the forearm. This system enables people with tetraplegia to independently stimulate their own hands to open or close, allowing grasp and release of a variety of manipulanda (pinch, squeeze, grasp, twist, lift, push, pull; see Figure 1). The patients thus use their hands to control the manipulanda and play computer games while practising different hand grasps. The games are graded according to hand function so even patients with severe upper limb paralysis can participate and, similarly, patients can play progressively more difficult games as they improve. The technology thus provides a way of encouraging patients to do large numbers of different hand movements within a dynamic environment. The primary aim of this trial therefore is to determine the effect on hand function of an intensive task-specific hand training program provided with FES through an instrumented exercise workstation. The secondary aim is to determine possible benefits on muscle strength, sensation, function, and quality of life.

**Figure 1 F1:**
[figure not shown]
**The instrumented exercise workstation (ReJoyce) demonstrating the different manipulanda**.

### Design

A multi-centre randomised controlled trial will be undertaken. One hand of each participant will be identified as the target hand. The target hand of participants will be randomised to the experimental or control group. Control participants will receive usual care while experimental participants will receive usual care plus an intensive 8-week program directed at the target hand. The trial will be conducted through seven SCI units in Australia and New Zealand. Ethical approval has been obtained from the Human Research Ethics Committee at each site and the University of Melbourne (HREC 0932764.1). Participants will be provided with information sheets and written informed consent will be obtained prior to recruitment and baseline assessment. Subject recruitment commenced December 2009 and will finish July 2011.

### Participants

Seventy-eight participants with recently-acquired tetraplegia undergoing inpatient rehabilitation in one of the seven participating SCI units will be recruited from a consecutive sample of admissions (see Figure 2). Therapists at each SCI unit will screen participants. One hand of each participant will be identified as the target hand according to the criteria below. In situations where both hands meet the inclusion criteria, the hand deemed most likely to benefit from intensive training by the treating therapist will be selected.

**Figure 2 F2:**
[figure not shown]
**Flow diagram of the trial**.

### Inclusion criteria

Participants will be included if they:

1. have sustained a SCI within the preceding 6 months

2. are currently receiving inpatient rehabilitation through one of the seven participating SCI units

3. will remain in the SCI unit for 12 weeks as part of standard rehabilitation

4. are 16 years of age or older and able to provide informed consent

5. have a motor complete or incomplete SCI at the neurological level of C2 to T1 (as per the International Standards of Neurological Classification for SCI)

6. have reduced ability to grasp with the target hand

7. are able to tolerate sufficient FES to enable the target hand to grasp and release

8. have the potential to benefit from the experimental intervention according to the judgment of the treating therapist

### Exclusion criteria

Participants will be excluded if they:

1. have any other type of neurological injury affecting the target hand (e.g. brachial plexus or peripheral nerve injuries)

2. have had trauma or surgery to the target hand or upper limb within the last 12 months

3. have had amputation of any digits on the target hand

4. are not able to sit out of bed for at least two hours per day over three consecutive days

5. have extensive fixed contractures in the upper limb of the target hand preventing use of the instrumented exercise workstation

6. have severe spasticity in the target hand or upper limb preventing use of the instrumented exercise workstation

7. are unable to attend the 6 month and 12 month follow-up assessments

8. are likely to undergo hand surgery in the target hand in the next year

9. are likely to experience autonomic dysreflexia or hypotension in response to FES

10. have any contraindications to FES such as cardiac pacemaker, epilepsy, forearm fracture or pregnancy

11. have intracranial metal implants

12. have impaired vision or are unable to view a computer screen

13. have any other serious medical condition likely to influence cooperation and adherence to the protocol including malignancies and psychiatric, behavioural or drug-dependency problems

### Randomisation

Participants will be randomly assigned to either control or experimental group with a 1:1 allocation as per a computer generated randomisation schedule stratified by site and the baseline score of the Action Arm Research Test (ARAT; <= 21 versus >21) using permuted blocks of random sizes. The block sizes will not be disclosed, to ensure concealment.

Prior to commencement of the trial, an independent researcher with no clinical involvement in the trial will use a computer random number generator to produce the randomisation schedule. Randomisation will occur after completion of baseline assessments by contacting an administrator independent of the recruitment process and located off site at Neuroscience Trials Australia, for allocation assignment. A participant will be considered to have entered the trial once his/her randomisation is revealed.

### Intervention

#### Control participants

Control participants will receive usual care and will not receive any electrical stimulation to the target hand or upper limb nor will they be exposed to the instrumented exercise workstation.

#### Experimental participants

In addition to the usual care provided to all participants, experimental participants will receive one hour of one-to-one hand training directed at the target hand with a research therapist, five times per week for 8 weeks. The training will consist of an intensive task-specific hand training program provided through an instrumented exercise workstation (ReJoyce) in conjunction with FES. The hand activities will involve playing computer games while practising functional tasks (including reaching, grasping, manipulating, pulling, rotating and releasing) using different manipulanda (see Figure 1).

The exercises and computer games will be progressed so that, as hand function improves, more difficult hand exercises and games will be introduced. Each training session will be one hour long and participants will be required to use the instrumented exercise workstation and FES as much as possible during this time.

The FES will be provided through 5 cm diameter electrodes embedded in wetted cloth pads backed with stainless steel mesh. The electrodes will be incorporated into a customised garment. The cathode of each electrode pair will be placed over the proximal end of each target muscle. The reference electrode will be placed on the dorsal surface of the forearm and just proximal to the wrist joint. The FES will be provided in trains of stimuli (50 per second: 200 μs biphasic, current-controlled pulses). The FES will be administered to any or all of the muscles that facilitate opening or closing of the hand including the flexors and extensors of the wrist, fingers and thumb.

FES will be triggered by participants clicking their teeth. The tooth clicks (vibrations) will be detected by a wireless earpiece, similar to a hearing aid, which sends a radio signal to the stimulator garment. This in turn stimulates the hand to open or close, allowing participants to grasp or release objects. The stimulator system has been tested and approved by the Canadian Standards Association. As it is not yet approved in Australia, the stimulator is being used for this trial under the Clinical Trials Notification Scheme of the Therapeutic Goods Administration of Australia.

If participants miss any treatments during the 8-week intervention period, the missed sessions will be offered to participants on weekends or during an optional additional week at the end of the 8-week intervention period.

#### All participants

All participants will continue to receive usual care for the hand and upper limb as typically provided by their SCI units. Usual care will be individualised to the needs of participants but will involve at least three 15-minute sessions per week of one-to-one therapy specifically directed at the target hand. This may consist of practising any or all of the following functional activities: moving checkers, grasping and releasing objects, manipulating objects, turning keys, pouring water and opening jars. In addition, all participants will receive any of the following as typically provided by participants' usual treating therapists as part of regular physiotherapy as well as vocational, recreational and occupational therapy:

• strength training

• training for activities of daily living (e.g. training for dressing, cooking or self care)

• computer-based games provided they only involve a headset, mouse or keyboard

• training in writing and the use of keyboards

• computer training (e.g. training in the use of word processors, internet or computer games)

• passive or assisted active movements (e.g. provided by therapists, family, carers or devices)

• stretches (e.g. provided by therapists, family, carers or devices)

• splinting (e.g. functional splints, resting splints, active-assist splints or hand orthoses)

• pressure garments or bandaging for oedema management or for the promotion of a passive tenodesis grip (e.g. JOBST gloves or pressure bandaging)

• arm ergometry

The use of computer games that involve hand and upper limb movement, for example games associated with Nintendo Wii^®^, PlayStation^® ^or similar equipment, will be limited where possible during the 8-week intervention period. There will be no restrictions past the 8-week intervention period.

#### Follow-up period

At the end of the 8-week intervention period, both experimental and control participants will continue to receive usual care up until the 12-month follow-up assessment. This may, or may not, involve sessions with a therapist. Therapy will not be standardised or restricted in any way. Instead, it will be left to the discretion of the treating therapists associated with the SCI units and care providers following discharge. The only restriction will be that neither experimental nor control participants use the instrumented exercise workstation. In addition, no participant will be permitted to practice any aspect of the outcome measures. They may, however, practice activities similar to those included in the hand tests as part of functional training.

#### Quality assurance

To ensure that the treatments are of a high standard and are delivered in accordance with the trial protocol, therapists responsible for administering the intensive training to experimental participants will attend a two-day workshop where they will be trained in the delivery of the treatment program. They will also be provided with a written protocol and standardised recording documents. In addition, all treatments provided to both experimental and control participants will be carefully recorded. For example, the following variables will be recorded during each treatment provided to experimental participants: therapy time, proportion of time spent with the stimulation activated, difficulty of games played and proportion of time spent playing games. Likewise usual care provided to both control and experimental participants will be recorded using a standardised form (the Spinal Cord Injury-Interventions Classification System)[11].

### Outcome assessments

Measurements will occur at baseline, 8 weeks after the commencement of the intervention period (8 weeks), and then at 6 months and 12 months after randomisation (see Table 1). There is a 3-week period after randomisation when all participants receive usual care prior to the commencement of the 8-week intervention period. This is to allow time for the delivery of the FES garments for experimental participants (these are custom made in Canada). For this reason, the 8-week assessments are 8 weeks after commencement of the intervention period but 11 weeks after randomisation.

**Table 1 T1:** Timeline of participants' progression through the trial

week -3	week -1	week 0	weeks 0 - 3	weeks 4 - 12	week 13 ^†^	weeks 14 - 25	week 26^§^	weeks 27 - 51	week 52^§^
screening	baseline assessment by blinded assessor	concealed random allocation	usual care for all participants^€^	8-week intervention **Exp**: Instrumented exercise workstation, FES and usual care **Control**: usual care	8-week assessment by blinded assessor	usual care for all participants	6-month assessment by blinded assessor	usual care for all participants	12-month assessment by blinded assessor

^† ^plus or minus 1-week window for commencement; 1-week window for completion upon commencement

^§ ^plus or minus 1-week window for commencement; 1-week window for completion upon commencement

^€ ^this 3-week period is to allow time for the ordering and delivery of the personalised FES garment for experimental participants

All assessments will be made by research therapists blinded to group allocation. Any inadvertent unblinding of assessors will be reported. In addition, the success of blinding will be estimated by asking assessors to guess participants' group allocations at the completion of each post-randomisation assessment.

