#### Modified Action Research Arm Test (ARAT) for the target hand at 8 weeks

The ARAT is a standardised measure of unilateral hand and upper limb function. It consists of four sub-tests including grasp, grip, pinch and gross movement. Participants will be required to perform every task in each subtest [12]. All tasks will be scored on a 4-point scale from 0 to 3 where 0 reflects poor hand function and 3 reflects good hand function. Scores will be summed to give a total possible score of 57 where a larger number reflects better hand function. The modified non-standardised table height will be used and testing will be done in a seated position. Although the ARAT was originally used as a measure of arm and hand function after stroke,[13] it has been successfully used in a trial similar to this one conducted in people with established SCI [personal communication; [name], 2009]. The ARAT has excellent reliability and has been validated against a number of other upper limb function tests [14-17]. It also has good face validity, assessing a range of functional hand tasks.

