#### Analysis

The primary analysis of ARAT score at 8 weeks will be performed using an ANCOVA model that includes treatment group and site as factors, and the baseline ARAT score as a covariate. All secondary outcomes (including the ARAT at 6 months and 12 months) will be analysed using a mixed model repeated-measures (MMRM) approach where applicable (i.e. where data are collected at 8 weeks, 6 months and 12 months). Multiple imputation analysis will be performed to account for the effect of missing data.

Analyses will be performed by a blinded and independent statistician according to the intention-to-treat principle and using the full dataset comprising all randomised participants. In addition, the primary analysis on the 8 weeks ARAT data will be repeated using a per protocol dataset. This dataset will only comprise participants who adhered to all aspects of the protocol and received at least 80% of training sessions (i.e., control participants who received at least 80% of the 15-minute sessions of one-to-one hand therapy and experimental participants who received this as well as 80% of the training sessions with the instrumented exercise workstation and FES). All analyses will be performed using Stata (Version 11 or higher).

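### The window on the primary 8-week ARAT opens before training is certain to be over, and the text and Table 1 disagree on how much training could be cut off

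*Protocol article*

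**What the plan says.** The protocol article fixes the timing of the primary outcome in several places.

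- **Endpoint.** The heading of the primary outcome is "Modified Action Research Arm Test (ARAT) for the target hand at 8 weeks".
- **Training.** Under Experimental participants, one-hour sessions are given "five times per week for 8 weeks". Missed sessions may be offered "on weekends or during an optional additional week at the end of the 8-week intervention period".
- **Delay before training.** Under Outcome assessments: "There is a 3-week period after randomisation when all participants receive usual care prior to the commencement of the 8-week intervention period".
- **Date of the primary assessment, text.** The same section says that "the 8-week assessments are 8 weeks after commencement of the intervention period but 11 weeks after randomisation".
- **Date of the primary assessment, Table 1.** The intervention column is labelled weeks 4 to 12 and the 8-week assessment is at week 13. The dagger on week 13 reads "plus or minus 1-week window for commencement; 1-week window for completion upon commencement". The 6- and 12-month visits have a footnote with the same wording.
- **Per-protocol set.** Under Analysis, it contains participants who "adhered to all aspects of the protocol and received at least 80% of training sessions". The article does not say that those sessions must come before the ARAT.

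**The concern.** The trial sets out to compare usual care with a complete 8-week programme. An end-of-treatment measurement should therefore not start while treatment may still be running. At 6 and 12 months a symmetric tolerance does no harm, because no trial training is running. At the 8-week visit the minus side reaches back into time that the article allows for training.

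Three things are at stake:

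- An experimental participant may be scored on the primary outcome with workstation sessions still to come. If later sessions add benefit, the estimated effect of the programme is diluted.
- Sessions given after the ARAT cannot have influenced it, yet they could count towards the 80% rule of the per-protocol set.
- Testing during continuing training might raise the risk of unblinding the assessor. This is an inference; the article does not describe where or how assessors work.

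The article gives two dates for the same visit, so the amount of training exposed cannot be read off without choosing between them.

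**Working it through.** **1. The plan's own sample size.** Inputs from Sample Size: effect 5.7 points, SD 14, correlation 0.8, two-sided alpha 5%, power 80%, drop-out 10%.

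- ANCOVA residual SD = 14 × √(1 − 0.8²) = 14 × 0.6 = 8.4.
- n per arm = 2 × [(1.960 + 0.842) × 8.4 / 5.7]² = 34.1, rounded up to 35.
- With drop-out: 35 / 0.9 = 38.9, rounded up to 39 per arm, 78 in total. The stated figure is reproduced.

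**2. Earliest permitted start against the end of training.** Planned sessions: 5 × 8 = 40.

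| | Table 1 | Text |
|---|---|---|
| Training starts (weeks from randomisation) | 4 | 3 |
| Eight weeks of training end | 4 + 8 = 12 | 3 + 8 = 11 |
| Nominal assessment | 13 | 11 |
| Earliest start (minus 1 week) | 12 | 10 |
| Core weeks outstanding at earliest start | 0 | 1 |
| Core sessions outstanding | 0 of 40 | 5 of 40 (12.5%) |
| Weeks to the end of the make-up week | 1 | 2 |

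The Table 1 column reads the labels as time points. If weeks 4 to 12 are counted inclusively, they span 12 − 4 + 1 = 9 calendar weeks. Eight weeks of training then fill weeks 4 to 11, and week 12 could be the make-up week, although the article does not say so. On either reading all 40 core sessions can be complete by the earliest start, and only make-up sessions are clearly exposed.

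The text column applies the one-week tolerance to the text's date. The footnote itself is attached only to week 13.

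**3. The conflict between the two clocks.** The text puts the visit at 3 + 8 = 11 weeks after randomisation; Table 1 puts it at week 13. Table 1 labels an 8-week period that follows a 3-week delay as weeks 4 to 12. These entries decide whether core training or only make-up training can fall after the ARAT.

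**4. Size on the text's clock.** Assumptions, neither given in the article: benefit is proportional to sessions received, and some share of experimental participants is assessed a full week early.

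- Effect at the earliest visit = 5.7 × 35/40 = 4.99 points.
- Average effect with share *s* early = 5.7 × (1 − 0.125*s*).
- Standard error = 8.4 × √(2/35) = 2.01.
- Power from the noncentral t distribution, 67 degrees of freedom:

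| Share assessed a week early | Mean effect | Power |
|---|---|---|
| None | 5.70 | 79.9% |
| A quarter | 5.52 | 77.3% |
| Half | 5.34 | 74.6% |
| All (upper bound) | 4.99 | 68.7% |

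A normal approximation gives 81.0%, 78.5%, 75.8% and 70.0%, the same pattern about one point higher. On Table 1's clock the loss is smaller, because only participants with missed sessions can have anything outstanding.

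**5. Per-protocol rule.** The threshold is 0.80 × 40 = 32 workstation sessions. A participant with 27 sessions before an early ARAT and 5 after it reaches 32 and meets that threshold, although the ARAT reflects 27/40 = 67.5%.

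**The case against.** The strongest reply concerns the anchor. The dagger belongs to week 13 in Table 1, and the sentence giving 11 weeks carries no tolerance. A reader might infer that core sessions are cut off whichever date is right, even when nobody misses a session. The article does not support that: on Table 1's dates the eight core weeks can be complete by week 12. This part of the reply stands, and the loss of 5 of 40 sessions applies only to the text's date.

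The reply also stands on size. Proportional benefit and the early shares are assumptions, the window equally allows late visits, and having everyone a week early is not a realistic use of a tolerance. Even the earliest visit on the text's clock leaves 35 of 40 sessions (87.5%), above the article's own 80% threshold. Any dilution runs towards no difference.

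A reader might also infer that an early visit costs controls nothing. It does cost them something: they receive at least three 15-minute hand sessions a week and are within six months of injury, so they lose therapy and recovery time too. What is specific to the experimental arm is the outstanding workstation training. On blinding, the article already plans to report inadvertent unblinding and to record assessors' guesses.

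Two further replies carry less weight. Booking rules may sit in the full protocol, but the footnote printed here is explicit, and it conflicts with dates printed beside it. A later window may also strain the 12-week stay required at entry, but Table 1 already permits a start in week 14.

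**Conclusion.** The point holds in a limited form. The minus side of the window lets the primary ARAT start in time that the article allows for training, on either clock, and nothing shown ties the visit to the end of training. On Table 1's dates the clear exposure is to make-up sessions; on the text's date it is one core week, 5 of 40 sessions. Which applies cannot be settled from the article.

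The expected effect is a modest dilution: about 2 to 3 points of power if a quarter of experimental participants are assessed a week early on the text's clock, about 11 points as an upper bound, and less on Table 1's clock. These figures rest on proportional benefit and on assumed shares. The sample size of 78 does not change. The correction is worth making because it is cheap and protects the primary endpoint, not because a large loss has been shown.

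**What to change.** - Reconcile the 11 weeks in the text, the week 13 and weeks 4 to 12 entries in Table 1, and the optional make-up week, so that one calendar counted from randomisation applies.
- For the 8-week assessment only, replace the plus-or-minus tolerance with a one-sided window of the same two-week width, opening no earlier than the end of the scheduled training period. Use the same calendar window from randomisation in both arms, and take the ARAT after any make-up sessions.
- Keep plus or minus 1 week at 6 and 12 months.
- In the per-protocol definition, count only sessions delivered before the ARAT towards the 80%.

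**Cost.** Consistent dates in the text and table, one footnote, and one line in the per-protocol definition. The average primary assessment moves up to about a week later in both arms. If Table 1's labels are time points and training ends at week 12, a two-week window from that point is weeks 12 to 14. Those are the start weeks already permitted, so the only change there would be that the ARAT waits for make-up sessions. Experimental participants who use the make-up week will fall later in the window than others, so visit dates should be compared between arms.
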